### Procedure

The study will be conducted with the use of *Nałogometr 2.0*, a mobile app designed to reduce craving and lapse risk in SUD and enhance post-treatment effects (available freely on Google Play and App Store). Prior to the first login, participants will be automatically navigated through all the necessary permissions and consents regarding data collection. Following the app installation, participants will be prompted with an onboarding questionnaire to collect demographic data. They will have a one-week window to complete the initial standardized questionnaire battery assessment. The responses from this initial assessment will serve as the baseline for subsequent evaluations throughout the study. The schedule of these assessments is outlined in **Figure 1**.

During a three-month period, participants will be required to engage in daily EMA assessments and to complete a monthly questionnaire battery. Concurrently, physiological data will be continuously gathered via smartbands.

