### Participants

The research will be conducted in collaboration with MONAR and AKMED, Polish organizations responsible for overseeing numerous addiction treatment clinics and centers, as well as other independent institutions. Recruitment of participants will target clinical patients who are undergoing either in-patient or out-patient treatment for Substance Use Disorder (SUD). For the in-patient cohort, the study will include individuals who are in the final stage of their therapy, specifically those expected to conclude their treatment within a maximum of 4 weeks but not fewer than 5 days. Eligible participants must be adults, aged 18 years or older, and must possess fluency in Polish. Moreover, in light of the study’s methodology, enrollment will be limited to users of iOS or Android smartphones.

Participants will be recruited into three groups: 1) Patients with alcohol addiction, 2) Patients with cross-addiction (alcohol and stimulants), 3) Patients with cannabis addiction. We plan on recruiting 150 participants with alcohol addiction, 150 participants with cross-addiction, and ~100 participants with cannabis addiction, due to lower availability of CUD therapeutic programs in Poland – and subsequently, less patients finishing therapy.

Each participant will be assigned to either experimental or control condition upon logging in to the mobile app for the first time.

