### Randomization

Upon their initial login to the mobile application, participants in each group (alcohol, cross-addiction, and cannabis), will be randomly allocated to either the experimental or control condition based on a code they receive during recruitment. Codes corresponding to experimental and control conditions were generated seperately for each group and then put in a randomized sequence. The randomization was done via an online randomization tool (45. [Online] Available from: https://www.sealedenvelope.com/simple-randomiser/v1/lists). Block sizes were determined using the simulation tool (45. [Online] Available from: https://www.sealedenvelope.com/randomisation/simulation/, taking into account planned sample sizes. Participants assigned to the experimental condition will gain immediate access to all psychological interventions following their initial app login. Those in the control condition will have access only to the daily EMA questions and the sobriety calendar, a tool for tracking their substance use. They will be provided access to the complete version of the app, including the psychological interventions, subsequent to the study’s conclusion - which is scheduled for 98 days after the first login.

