Participants assigned to the intervention group will be granted immediate access to all intervention modules upon logging into the app using their unique code. They will have the autonomy to interact with any of the interventions at their discretion without any mandatory commitment. Adherence to a stringent schedule for engaging with the interventions is not a prerequisite for participants in the intervention condition.

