## Results

### Hypotheses

The primary outcomes of this study are centered on the hypothesis that participants receiving the intervention, as opposed to those in the control condition, will exhibit reduced levels of craving and fewer lapses at the one-month follow-up post-app implementation relative to their baseline levels. It is anticipated that this downward trend in craving and lapse incidents will be sustained throughout subsequent evaluations. Additionally, it is conjectured that a single session of self-guided psychological intervention may yield a notable decrement in both craving intensity and the risk of a lapse occurring. Furthermore, the hypothesis extends to posit that participants in the intervention condition will demonstrate lower levels of substance addiction, reduced symptoms of anxiety and depression, and an elevated sense of life satisfaction when compared to those in the control group, as measured by the relevant standardized questionnaires.

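### The questionnaire baseline may be completed up to a week after the experimental arm has been given all modules, so it can already contain treatment effect in one arm only

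*Protocol article*

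**What the plan says.** **Allocation.** The Participants section states: "Each participant will be assigned to either experimental or control condition upon logging in to the mobile app for the first time". The Randomization section adds that participants "will be randomly allocated to either the experimental or control condition based on a code they receive during recruitment".

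**Exposure.** Under Randomization: "Participants assigned to the experimental condition will gain immediate access to all psychological interventions following their initial app login". Mobile application content repeats this and sets no order or schedule of use: "They will have the autonomy to interact with any of the interventions at their discretion without any mandatory commitment". Over the same period controls have only the daily EMA questions and the sobriety calendar.

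**Baseline.** Onboarding starts at the first login (Measures). The standardized battery follows it in the first week (Study design). The Procedure section says: "They will have a one-week window to complete the initial standardized questionnaire battery assessment", and then: "The responses from this initial assessment will serve as the baseline for subsequent evaluations throughout the study".

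**Use of baseline.** The Hypotheses section frames the primary hypothesis on craving and lapses as a difference at one month compared with baseline. Data analysis compares battery scores between arms across measurements in mixed-effects models. It limits the secondary analysis to participants with a completed baseline and at least one later assessment.

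**Expected speed of effect.** The Hypotheses section conjectures that "a single session of self-guided psychological intervention may yield a notable decrement in both craving intensity and the risk of a lapse occurring".

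**The concern.** A baseline is useful because treatment cannot have influenced it. Here one arm may have had the full intervention for up to a week before the value is recorded, and the other arm has not. By the authors' own conjecture, a single session is enough to matter. Any early benefit in the experimental arm then sits in the reference value, and an analysis of change from that value removes it from the estimate.

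The secondary analysis set raises a second problem. Because the battery comes after allocation, and the arms see different app content in that week, completing it could differ by arm. Conditioning on completion then no longer compares the groups as randomised.

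The Discussion is prepared for only small effects, so a bias towards no difference is unwelcome. A later analysis plan cannot create a pre-exposure measurement that was never taken.

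**Working it through.** **Order of events, from the text**

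1. Day 0: first login. The condition takes effect and the modules open in the experimental arm (Participants, Randomization, Mobile application content).
2. Day 0: onboarding starts, covering demographics and substance-use history, including frequency and periods of abstinence (Measures).
3. From onboarding to about day 7: the baseline battery is completed (Study design, Procedure).
4. One, two and three months: follow-up batteries. Controls receive the full app 98 days after first login.

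No sentence withholds the modules until step 3 is done. The longest possible exposure before baseline is 7 days, which is 7/98 = 7% of the study and 7/30 = 23% of the first month. This is a maximum, not an expected value.

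**The plan's own figure.** The sample size section gives at least 360 participants for 80% power on a group effect. It describes the effect only as small and gives no alpha, intraclass correlation or number of measurements, so 360 can be neither confirmed nor refuted. Several plausible sets of inputs come close to it. It is used below only as a reference point.

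**Attenuation.** Let D be the effect at follow-up and f the fraction of it already present when baseline is recorded.

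- Change from baseline, or a group-by-time contrast: D - fD = (1 - f)D.
- Baseline as covariate with slope b: D - b·fD = (1 - b·f)D.
- Follow-up values compared between arms without baseline: D, unchanged.

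**Power illustration.** Assume a two-sided alpha of 0.05, 1:1 allocation and an effect that gives exactly 80% power at 360. With 180 per arm that effect is (1.960 + 0.842) × √(2/180) = 0.295 SD. If the estimate is multiplied by k, power = Φ(2.802·k - 1.960). The last column is the total number that restores 80% for a change contrast.

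| f (assumed) | k, change | Power, change | k, adjusted (b = 0.5) | Power, adjusted | Total N, change |
|---|---|---|---|---|---|
| 0 | 1.00 | 80% | 1.00 | 80% | 360 |
| 0.1 | 0.90 | 71% | 0.95 | 76% | 446 |
| 0.2 | 0.80 | 61% | 0.90 | 71% | 564 |
| 0.3 | 0.70 | 50% | 0.85 | 66% | 736 |

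The documents give no value for f or b; both are assumptions. The last column shows the scale of the loss and is not a proposed sample size.

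**The case against.** **Scope.** The one-week window governs the questionnaire battery, which feeds the secondary outcomes. The primary outcomes, craving and lapses, are monitored by daily EMA, for which an interrupted time series is planned; nothing says the battery is subtracted from them or adjusted for. This stands. Extending the point to EMA craving is an inference: the primary hypothesis refers to baseline levels, EMA is delivered through the app, and no craving value before login is described. Substance-use history is collected at onboarding, so some information on use is available at login.

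**Contamination is possible, not shown.** Module use is voluntary, and many participants may complete the battery before opening a module. Figure 1 holds the assessment schedule and is not shown, so a gate cannot be fully excluded, although immediate access speaks against one. Likewise, the trial is declared participant-blinded, so differential completion of the battery is a risk and not an observed fact.

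**Size.** A reader might infer that the trial loses most of its power; f = 0.5 with a change score would give 29%. The documents do not support that figure. They supply no f, name neither a change-score nor a baseline-adjusted estimator, and state the 80% for a group effect in a random-intercept model. A group effect averaged over measurements need not shrink as a group-by-time contrast does.

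**Remedy.** A reader might also infer that any battery completed after the first module opening should be set to missing. Controls have no modules during the study, so that rule could delete baselines only in the experimental arm. Combined with the completed-baseline requirement, it would exclude early users from one arm and create the very selection at issue.

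**Conclusion.** The point holds for the questionnaire baseline. As written, that baseline can be recorded after up to a week of treatment access in one arm only. Any contrast that uses it as a reference is then biased towards no difference, and the completed-baseline requirement selects participants after allocation. For EMA craving the concern is a reasonable inference, not something the quoted window itself shows.

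The size cannot be derived from the documents. Under the assumption f = 0.1 to 0.3, a nominal 80% power becomes about 71% to 50% for a change contrast, or 76% to 66% with baseline adjustment at slope 0.5. These figures also assume a two-sided alpha of 0.05 and equal allocation. A between-arm comparison of follow-up values is unaffected by this attenuation. No change in sample size follows.

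**What to change.** **For new participants.** Have the app activate the assigned condition, in both arms alike, only after the baseline battery and one baseline EMA craving entry have been submitted. Keep the arm of each code concealed until then and count allocation from activation.

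**For participants already enrolled.** Do not set late baselines to missing, and do not exclude anyone from the secondary analysis for lacking a baseline. Use app timestamps to record first module use relative to completion of the battery, and report it. Add a sensitivity analysis that compares follow-up values between arms, as randomised, without the post-allocation baseline.

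**Cost.** A small change in app logic and a sentence or two in the protocol. Some people may stop before activation. They would leave before allocation and would not bias the comparison, provided the arm of the code is truly concealed; this matters because codes tied to an arm are handed out at recruitment.

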### Mobile application content

The Nałogometr 2.0 app, available at https://nalogometr.pl/, is designed for individuals seeking to decrease or discontinue their problematic substance use or behavioral habits. The app provides features such as Ecological Momentary Assessment (EMA) and self-guided psychological interventions. For the duration of the study, the accessibility of various modules within the app will be contingent upon the participant’s assigned condition—the control group will not have access to the app’s full capabilities until after the conclusion of the study.

*Dashboard.* The app features a user-friendly dashboard designed for simplicity and ease of navigation, granting users swift access to psychological interventions, EMA modules, and a sobriety calendar, which allows for tracking participants’ substance use.

*Intervention modules.* The application encompasses a suite of self-guided psychological intervention modules. These interventions include a series of audio-guided sessions that focus on gratitude, thoughts management, motivation, relaxation, along with mindfulness sessions aimed at heightening awareness of emotions and bodily signals, and managing stress. These audio sessions are in line with other empirically evaluated self-guided audio exercises (46–48). Furthermore, the intervention module of the app also incorporates CBT-based written exercises that are rooted in thought management and journaling techniques. These are designed to bolster self-confidence and self-efficacy, as well as to deepen the user’s understanding of the interplay between situational triggers, mood, and sobriety. We included longterm intervention modules based on CBT components, e.g., *My beliefs* which is a thought management technique, *Thinking traps*, another thought management and reframing technique, *Planner*, intended to improve goal achievement and self-efficacy, *Mood Journal*, where users are instructed to better understanding of the relationship between situations, thoughts, mood and sobriety, *Dream diary* and *Success diary* intended to enhance self-observation, self-esteem, self-confidence, and awareness of emotions, and *Gratitude Journal* which improves the positive attitude towards yourself, people and world.

Participants assigned to the intervention group will be granted immediate access to all intervention modules upon logging into the app using their unique code. They will have the autonomy to interact with any of the interventions at their discretion without any mandatory commitment. Adherence to a stringent schedule for engaging with the interventions is not a prerequisite for participants in the intervention condition.

### Measures

During the onboarding process—initiated at the first login—participants will be prompted to provide sociodemographic information, including gender, age, place of residence, and details of their addiction profile. They will also respond to questions about their history of substance use, encompassing aspects like the substance involved, duration of use, frequency, treatment history, and periods of abstinence. A series of standardized questionnaires (refer to **Table 1** for an overview) will be employed to gather data on a range of psychological variables. These questionnaire batteries will be administered at one, two, and three months into the study, facilitating the collection of longitudinal data.

**Table 1 T1:** Measures used in questionnaire assessment.

	Group 1 (cross-addiction)		Group 2 (alcohol addiction)		Group 3 (cannabis addiction)	
Measures	Baseline	Monthly assessments	Baseline	Monthly assessments	Baseline	Monthly assessments
*Socio-demographic questions*	**x**		**x**		**x**	
*Onboarding questions*	**x**		**x**		**x**	
Substance use-related measures						
*Dependence severity* (Screener)	**x**	**x**	**x**	**x**	**x**	**x**
*Substance dependence* (SDS)	**x**	**x**	**x**	**x**	**x**	**x**
*Alcohol dependence* (AUDIT)	**x**	**x**	**x**	**x**	**x**	**x**
*Stimulants dependence* (DUDIT)	**x**	**x**				
*Cannabis dependence* (CUDIT-R)					**x**	**x**
Psychological functioning measures						
*Anxiety and depression* (HADS)	**x**	**x**	**x**	**x**	**x**	**x**
*Coping with stress* (mini-COPE)	**x**	**x**	**x**	**x**	**x**	**x**
*Sensation seeking* (BSSS)	**x**	**x**	**x**	**x**	**x**	**x**
*Emotional regulation* (DERS)	**x**	**x**	**x**	**x**	**x**	**x**
*Impulsivity* (SUPPS)	**x**	**x**	**x**	**x**	**x**	**x**
*Life satisfaction* (SWLS)	**x**	**x**	**x**	**x**	**x**	**x**

EMA will be conducted daily to monitor cravings and lapses. The EMA will also record additional variables that are associated with craving intensity, such as current mood, arousal, stress, anxiety, loneliness, fatigue, anger, hunger, and uncertainty.

### Primary outcomes

Primary outcomes of interest will include self-reported number of lapses and addiction craving (intensity of the urge to use a substance at a moment of assessment).

### Secondary outcomes

During the monthly questionnaire assessment, following measures will be applied:

*Substance use.* Self-report psychological measures of substance dependence will be administered across all participant groups. The assessment will include the Severity of Dependence Scale (SDS) (49), which measures dependence on psychoactive substances. Additional questionnaires will be presented depending on the type of addiction. For group A (patients with Alcohol Use Disorder) assessment will include the Alcohol Use Disorders Identification Test (AUDIT) (50). In group B (patients with cross-addiction – alcohol and stimulants) we will administer both AUDIT and the Drug Use Disorders Identification Test (DUDIT) (51). Group C (patients with Cannabis Use Disorder) will complete the Cannabis Use Disorders Identification Test-Revised (CUDIT-R) (52).

*Depression and anxiety.* Symptoms of depression and anxiety among the participants will be quantified using the Hospital Anxiety and Depression Scale (HADS) (53). This instrument is a 14-item questionnaire divided into two subscales: one for anxiety and one for depression, each comprising 7 items. For both subscales, a score ranging from 8 to 10 suggests mild symptoms of depression or anxiety, while scores between 11 and 21 signify the potential presence of a depressive or anxiety disorder.

*Emotion regulation and coping with stress.*Emotion regulation will be evaluated using the Difficulties in Emotion Regulation Scale (DERS) (54), which is a 36-item questionnaire. Participants will rate items on a scale from 1, indicating ‘almost never’, to 5, signifying ‘almost always’. The DERS is organized into six subscales, each designed to assess different facets of emotion regulation difficulties.

For assessing stress management, the Coping Orientation to Problems Experienced (mini-COPE) questionnaire will be used (55). This instrument includes 28 items referring to various coping strategies individuals employ in response to stress.

*Impulsivity and sensation seeking*. Impulsivity will be quantified utilizing the short version of the Impulsive Behavior Scale (SUPPS) (56), which is composed of five subscales. Each subscale contains four items. To assess sensation seeking, the study will employ the 8-item Brief Sensation Seeking Scale (BSSS) (57).

*Life satisfaction*. Life satisfaction will be measured with a 5-item Satisfaction with Life Scale (SWLS) (58).

### Engagement metrics

To assess participant engagement with the Nalogometr application and its components, several metrics will be tracked throughout the study period.

*Average number of days of app usage during the study*: Participants’ engagement with the Nalogometr application was measured by recording the average number of days they accessed the app during the study period. This metric provides an overview of participants’ overall engagement levels throughout the intervention.

*Average number of days of app usage per week*: In addition to the total number of days of app usage, we calculated the average frequency of app usage per week for each participant. This allowed us to assess the consistency of participants’ engagement with the application over time.

*Average number of reminders responded to by the user*: The Nalogometr application includes reminder features aimed at promoting engagement with the intervention components. We tracked the average number of reminders responded to by participants throughout the study, both overall and within specific timeframes.

*Average number of completed interventions:* For participants assigned to the intervention group, the completion of interventions within the Nalogometr application was tracked. We calculated the average number of completed interventions over the study duration and within specific timeframes to evaluate participants’ engagement with the intervention components.”

## Results

### Hypotheses

The primary outcomes of this study are centered on the hypothesis that participants receiving the intervention, as opposed to those in the control condition, will exhibit reduced levels of craving and fewer lapses at the one-month follow-up post-app implementation relative to their baseline levels. It is anticipated that this downward trend in craving and lapse incidents will be sustained throughout subsequent evaluations. Additionally, it is conjectured that a single session of self-guided psychological intervention may yield a notable decrement in both craving intensity and the risk of a lapse occurring. Furthermore, the hypothesis extends to posit that participants in the intervention condition will demonstrate lower levels of substance addiction, reduced symptoms of anxiety and depression, and an elevated sense of life satisfaction when compared to those in the control group, as measured by the relevant standardized questionnaires.

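### The primary hypothesis is worded as a change from baseline, but no value of craving or lapses is scheduled before the experimental arm receives the modules

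*Protocol article*

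**What the plan says.** The Primary outcomes section names two outcomes: "Primary outcomes of interest will include self-reported number of lapses and addiction craving". The Hypotheses section says that intervention participants, in contrast to controls, "will exhibit reduced levels of craving and fewer lapses at the one-month follow-up post-app implementation relative to their baseline levels", and expects the decline to persist at later evaluations.

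Baseline is defined under Procedure, where the initial questionnaire battery is introduced: "They will have a one-week window to complete the initial standardized questionnaire battery assessment". The next sentence reads: "The responses from this initial assessment will serve as the baseline for subsequent evaluations throughout the study".

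The primary outcomes are collected elsewhere. Under Measures: "EMA will be conducted daily to monitor cravings and lapses". Onboarding, also under Measures, takes a substance-use history, "encompassing aspects like the substance involved, duration of use, frequency, treatment history, and periods of abstinence".

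Under Randomization: "Participants assigned to the experimental condition will gain immediate access to all psychological interventions following their initial app login". The Mobile application content section repeats that access is immediate and adds that use of the modules is at the participant's discretion.

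**The concern.** A hypothesis about change needs a starting value for the outcome that changes. Here the defined baseline and the primary outcomes do not meet: one is a questionnaire battery, the other a stream of daily entries that begins in the app when the modules are already open to one arm.

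The natural substitute is the first few days of EMA. In the experimental arm those days can follow module use. The Hypotheses section itself conjectures that a single session may noticeably lower craving and lapse risk, so on the protocol's own reasoning an early-EMA baseline may contain treatment effect. Subtracting it from the month-1 value removes real effect and pulls the comparison toward no difference.

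For lapses there is a second problem. In-patients are enrolled with between 5 days and 4 weeks of treatment left. If they start at or near zero, an app that works would slow a rise after discharge. It would not produce the decline that the hypothesis describes.

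**Working it through.** **1. Where each quantity is measured.** Table 1 has 13 rows: socio-demographic questions, onboarding questions and 11 instruments. None is labelled momentary craving or lapse count. The onboarding topics named include frequency of use and periods of abstinence, but neither primary outcome. Craving and lapses are assigned to daily EMA. EMA runs in the app, entered with the code that also opens the modules. No EMA period before access is described.

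**2. The plan's own figure.** Sample size calculation gives 360 participants for 80% power to detect a group effect, from a simulation with a small effect of unstated size. The inputs are not given, so 360 can only be bracketed. At two-sided alpha 0.05 (assumed), a single-measure comparison needs 786 in total at 0.20 SD, 504 at 0.25, 362 at 0.295 and 350 at 0.30. With 0.20 SD and repeated measures under a random intercept, 360 corresponds to an intraclass correlation of about 0.28 (4 measures) or 0.44 (30 measures). The figure is compatible with a small effect. The point here does not depend on it, except that the target is a group effect and not a change from baseline.

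**3. What a contaminated baseline costs (illustration).** Assumptions: n = 180 per arm (360/2), month-1 effect δ = 0.295 SD, correlation r between baseline and month 1, and a share c of the effect already present in the baseline. The SD of a change score is √(2(1−r)). Power = Φ(δ(1−c)/SD × √(n/2) − 1.96), with √(180/2) = 9.487.

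For r = 0.5, SD = 1:
- c = 0: 0.295 × 9.487 = 2.799; Φ(0.839) = 79.9%
- c = 0.25: 0.22125 × 9.487 = 2.099; Φ(0.139) = 55.5%

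| Share of effect in baseline | r = 0.5 | r = 0.7 |
|---|---|---|
| 0 | 79.9% | 95.1% |
| 25% | 55.5% | 77.3% |
| 50% | 28.8% | 43.9% |

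Comparing the arms at month 1 with no baseline gives 79.9% whatever r is. A clean pre-access value used as a covariate, with SD √(1−r²), gives 89.8% (r = 0.5) or 97.5% (r = 0.7).

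**4. How large c might be.** If the effect grew linearly to d over 30 days, its mean over days 0 to 7 would be (3.5/30)d = 0.117d. That is about 12% of the day-30 effect, or 0.117/0.5 = 23% of the mean effect over the month. An effect present in full from the start would give c = 100%. Both shapes are assumptions.

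**5. The floor for lapses.** No baseline lapse rate is given. If first-week lapses were Poisson with mean 0.02, 0.1 or 0.5, then e^(−mean) = 98%, 90% or 61% of participants would start at zero and could not fall. For such a participant, change from baseline equals the later count, so the between-arm difference is unharmed. What fails is the description of success as a decline.

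**The case against.** The strongest reply is that the hypothesis already contrasts the randomised arms. The Primary outcomes section names lapses and craving without reference to baseline, and the sample size rests on a group effect. A between-arm comparison after randomisation needs no baseline. This stands. A reader might infer that the endpoint has no valid starting value and so cannot be confirmed or refuted. The documents do not support that, because the randomised contrast can be tested whatever is decided about baseline.

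A reader might also infer that lapses can only stay level or rise in both arms. That goes too far. The article gives no lapse rate, states the final-stage rule for in-patients only, also recruits out-patients, and lists no abstinence criterion. Starting near zero is a plausible inference for in-patients and no more.

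Three further points deserve weight. Access is not exposure: module use is voluntary, so some early entries will precede any session, and the size of the contamination is unknown. The content of the onboarding questions and the dependence screener is not given, and the onboarding list is illustrative, so a usable recent-use measure may already exist. The assessment flowchart is not shown, the preregistration is not at hand, and an article may leave the choice of baseline EMA days to an analysis plan. That last point does not dispose of the matter. With modules open from login and no earlier EMA described, whichever EMA days are chosen can fall after exposure.

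**Conclusion.** The point holds as a fault in how the primary contrast is stated. The article words it as change from baseline, defines a baseline that lists neither primary outcome, and opens the modules before any EMA value is scheduled. A change score built on early EMA is liable to be biased toward no difference.

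The size cannot be fixed from the article. Under the assumptions shown, a quarter of the effect in the baseline costs about 24 points of power at r = 0.5 (79.9% to 55.5%) and about 18 at r = 0.7 (95.1% to 77.3%). The direction rests on the intervention acting early, which the protocol itself conjectures.

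For lapses, the expected decline suits in-patients still in treatment poorly, on the inference that they start near zero. This is a fault of wording and does not bias the between-arm comparison. The change should be made, but the trial's main comparison is not invalidated.

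**What to change.** - State the primary contrast as the between-arm difference in mean EMA craving and in lapse rate over month 1 after first login. This matches the group effect on which the sample size rests.
- Remove the reference to baseline levels from the primary hypothesis, and drop the expectation of a continuing decline as a criterion for lapses.
- Add the EMA craving item to onboarding, together with a question on days of use in the past 30 days if the existing frequency item does not already supply this. Both should be answered before the modules unlock and used only as covariates.

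The rewording costs nothing in data and applies to participants already enrolled. The two items take about a minute per participant. Those already enrolled would lack these covariates, so the covariate-adjusted analysis would have to allow for their absence.
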